### Secondary outcome measures

Secondary outcomes measures aim at exploring the impact of the DECISION+ program on the decision making processes and the optimal use of antibiotics in the context of ARI. These measures include:

#### Decision to use antibiotics

After each clinical encounter for ARI, both patients and their FPs/GPs indicate if it was decided to: 1) use antibiotics, 2) delay antibiotics or 3) not use antibiotics.

#### Decisional conflict

After each clinical encounter for ARI, both patients and physicians complete the Decision Conflict Scale. This scale includes 16 items, each item being scored on a 5-point Likert scale (1 = strongly agree to 5 = strongly disagree) with higher score associated with higher decisional conflict. Internal consistency coefficients (Cronbach's alpha) from previous studies ranged from 0.78 to 0.92 in the patients' version and from 0.78 to 0.90 in the physicians' version [23,24].

#### Decisional regret

One to two weeks after clinical encounter, patients complete the Decisional Regret Scale over the phone (Cronbach's alpha = 0.81 to 0.92 in previous studies) [25].

#### Prescription profile of antibiotics in ARI

Prescription profile of all FPs/GPs from the Quebec City area, including all physicians participating in the study, is established using the Régie de l'Assurance Maladie du Québec (RAMQ) databases. Data are restricted to patients covered by the public prescription drug insurance of the Province of Quebec (about half of the total population in the province). Type of antibiotics prescribed and date of prescription filling are matched with the reasons for encounter (for an ARI) as stated by physicians for billing purpose. Data collection extends from 3 months before the beginning of the study to 3 months after the end of the study.

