## Background

Most health decisions occur in context of scientific uncertainty, the "grey zone" of decision making, and making decisions about the use of antibiotics for acute respiratory infections (ARI) is no exception [1]. ARI are the most frequently reported reasons for consulting a primary care provider in North America and include acute otitis media, acute rhinosinusitis, acute pharyngitis, and acute bronchitis. Together, these infections, excluding pharyngitis but including chronic sinusitis and eustachian tube disorders account for 5.7% of the primary diagnosis groups for adults and reach a total of 16.3% for children under the age of twelve in community based practices [2]. Although each type of ARI has distinct features, they all share in common that a large proportion of those infections are viral. Indeed, only 38% of adults with rhinosinusitis, 6% to 18% of children with ARI, and 5 to 15% of adults with pharyngitis have a bacterial infection [3,4]. Nonetheless in North America, although it varies according to the specific type of ARI [5-13], the use of antibiotic is estimated to be 63% to 67%, well above the expected prevalence of bacterial infections [5,7-11,14-17].

As suggested above, diagnostic and management of ARI are ripped with uncertainty. The probabilistic nature of the diagnosis of ARI makes it difficult for both the physician and the patient to choose the "best" course of action and is associated with prescription of antibiotics [18]. Scientific evidence that imparts conflicting results regarding treatment options (i.e. balance between risks and benefits) or the absence or insufficiency of scientific evidence makes this choice even more difficult [19]. Moreover, the probabilistic aspect of the evidence that is drawn from populations implies uncertain outcomes for the individual [20]. Consequently, patients and physicians need help in addressing their decisional needs and in resolving uncertainty when making decisions about the use of antibiotics for ARI, the most frequent "grey zone" health decisions in primary care.

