#### Interactive workshops

Three 180-minute workshops are offered to participating FPs/GPs. Each one addresses a key component of our conceptual framework (Figure 1). The first workshop focuses on the probabilistic nature of the diagnosis of a bacterial vs. viral ARI. The second workshop focuses on the available evidence regarding the balance between risks and benefits when facing decision about the use antibiotics or not in ARI. It also addresses effective strategies to communicate this information to a patient. The third workshop focuses on strategies to foster active participation of patients in the decision-making process.

All three workshops include videos that facilitate group discussion about perceived barriers and facilitators to implementing SDM in the context of the use antibiotics for ARI. All workshops are offered at the FMG clinical site and leaded by experienced trainers (co-PI and co-I). Participants receive a toolkit including the material from the training workshops and a series of decision support tools to help them communicate with their patients the probability of a bacterial vs. viral ARI and the risks and benefits associated with the use of antibiotic in ARI. These decision support tools also include a section to help clarify patient's values regarding the use of antibiotics in ARI. All workshops are audio-taped to ensure fidelity of the intervention across FMG.

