#### Feedback

Results of score agreement on the Decisional Conflict Scale between patients and physicians, as measured during the patient recruitment periods before the first workshop (Phase 1 in the experimental group and Phase 1 and 2 in the control group – see Figure 2), are provided to participating FPs/GPs in a personalized sealed envelope at the beginning of the third workshop. Physicians are also provided with pooled results from their colleagues. Time is provided during the workshop to explain how to interpret the results and for group discussion. A personalized and group prescription profile related to antibiotic prescribed to patients consulting with ARI is provided at the end of the series of workshops.

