#### Script Concordance Test (SCT)

Clinical reasoning is assessed with a SCT on diagnosis and management of ARI [26-31]. The same SCT is completed three times over the study period (Figure 2). In both groups, SCT are completed at the beginning of the first and at the end of the third workshop (SCT 1 and 2 in the experimental group and SCT 2 and 3 in the control group). SCT 1 in the control group is completed at baseline and SCT 3 in the experimental group at exit of the study.

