### Sample size and analysis

The objective is to recruit four FMG (at least 24 physicians and a total of 360 patients with an ARI that is 5 patients per physician in each one of the three recruitment phases) for this pilot clustered RCT. This study is a feasibility study and therefore no sample size calculation was performed. Our design allow a comparison of physicians (and patients) data randomly exposed or not to the DECISION+ program (RCT) and a comparison of before and after data combining the results of the immediate and delayed exposure to the DECISION+ program.

It is not possible to blind participating FPs/GPs from the planned intervention but individuals involved with data analyses will be blinded to group allocation and initial results will be provided to researchers without revealing group allocation. Statistical analysis for the primary outcome feasibility measures will be performed using proportions and means and associated 95% confidence intervals. Methods for assessing the statistical significance of the secondary outcome measures between study groups will take into account the clustered nature of the dataset.

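### The RAMQ antibiotic profile selects data by a billed ARI label that training could shift, so an arm difference need not mean a change in prescribing

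*Protocol article*

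**What the plan says.** Under Prescription profile of antibiotics in ARI, the protocol article takes the type of antibiotic and the fill date from RAMQ data for publicly drug-insured patients. These "are matched with the reasons for encounter (for an ARI) as stated by physicians for billing purpose". The profile covers all family physicians in the Quebec City area, from 3 months before the study to 3 months after it.

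Other sections bear on the label that selects these data:

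- Interactive workshops: "The first workshop focuses on the probabilistic nature of the diagnosis of a bacterial vs. viral ARI".
- Script Concordance Test: "Clinical reasoning is assessed with a SCT on diagnosis and management of ARI". The article thus treats diagnostic reasoning as something to be measured over the study.
- Feedback: "A personalized and group prescription profile related to antibiotic prescribed to patients consulting with ARI is provided at the end of the series of workshops".
- Sample size and analysis: "It is not possible to blind participating FPs/GPs from the planned intervention". The same section plans significance assessments of secondary outcomes between study groups.

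The effect on the prescription profile is one of the specific aims in the Background, and the abstract names the profile as a secondary outcome. The article describes no antibiotic measure from RAMQ that is independent of the ARI label.

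**The concern.** A visit enters the profile only if the treating physician bills it as an ARI. That decision comes after allocation, and the person making it knows the allocation and, in one arm, has been trained in ARI diagnosis. Selecting data on something the intervention may alter breaks the protection of randomisation for that comparison. If trained physicians bill some borderline visits under another reason, or bring others in, the two arms' profiles describe different mixes of visits.

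At stake is the conclusion on the prescription-profile aim. A coding change could create an apparent effect or hide a real one, and a pilot meant to prepare a larger trial on antibiotic use would pass the same measure forward. The between-arm risk applies while only the immediate group has been trained. After that it carries into the pooled before-after comparison.

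**Working it through.** **The plan's own figure.** 4 FMG × 6 physicians = 24 physicians, and 24 × 5 patients × 3 phases = 360 patients, as stated in Sample size and analysis. The point does not depend on these numbers.

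**Inputs.**
- Antibiotic use in ARI, p: 63% to 67% (Background).
- Form of the profile: the article states no rate, so I assume the proportion of ARI-billed visits with a filled antibiotic.
- Relabelled share, s: not in the documents. I assume 5%, 10% and 20%.

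**Formulas.** Take 100 ARI-billed visits, with T = 100p treated and U = 100(1 − p) untreated. Prescribing is held fixed and only the billed label changes.

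- (a) A share s of untreated visits leaves the label: T / (T + U(1 − s))
- (b) A share s of treated visits leaves: T(1 − s) / (T(1 − s) + U)
- (c) Untreated visits enter, 100s in number: T / (100 + 100s)
- (d) Treated visits enter, 100s in number: (T + 100s) / (100 + 100s)

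In (a) and (b), s is a share of the untreated or treated visits. In (c) and (d) it is a share of all the initial ARI visits.

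**Change in the profile, in percentage points, over p = 63% to 67%.**

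| Route | s = 5% | s = 10% | s = 20% |
|---|---|---|---|
| (a) untreated leave | +1.1 to +1.2 | +2.3 to +2.4 | +4.7 to +5.0 |
| (b) treated leave | −1.1 to −1.2 | −2.4 to −2.5 | −5.1 to −5.3 |
| (c) untreated enter | −3.0 to −3.2 | −5.7 to −6.1 | −10.5 to −11.2 |
| (d) treated enter | +1.6 to +1.8 | +3.0 to +3.4 | +5.5 to +6.2 |

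Examples: route (c) at 65% and s = 10% gives 65/110 = 59.1%, a fall of 5.9 points. Route (d) at 63% and s = 20% gives 83/120 = 69.2%, a rise of 6.2 points.

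**If the profile is a count.** If 10 of 65 treated visits are re-coded, the count of ARI-matched fills drops from 65 to 55 although nobody prescribes less.

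**With a label-independent denominator.** If the denominator is all visits by drug-insured patients, relabelling alters neither the fills nor the visits, so the rate changes by 0 points.

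**The case against.** The strongest objection is that the workshop deals with bacterial versus viral disease within ARI. A visit reclassified from bacterial to viral is still an ARI visit and stays in the profile. This stands as a limit. A reader might infer that the programme teaches physicians how to label or bill ARI visits, but no section mentions billing or coding. The overall profile moves only if visits cross the outer boundary of the ARI codes, and the article does not give that boundary. The Background says that ARI "include acute otitis media, acute rhinosinusitis, acute pharyngitis, and acute bronchitis", but this is epidemiology and not an outcome definition. A broad code set would shrink the effect. The code list is detail that an article may leave to the full protocol, so its absence is not a fault.

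The size is also open to challenge. A reader might count 10 relabelled visits per 100 and conclude that the profile would be off by −6 to +7 points. The +7 comes from 65/90 = 72.2%, which means moving 10 of 35 untreated visits, or 29% of them. Nothing in the documents supports that rate, or any other.

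Feedback of the personal profile is a weak argument for a difference between arms. Both arms eventually receive the programme, and the article does not say when physicians are told that a profile will come.

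Existing features help but do not settle the matter. The pre-study window gives a baseline and the area-wide data give untrained comparators, yet neither removes a coding change that starts with training in one arm. The antibiotic decision recorded at each encounter does not use billing codes, but it covers only recruited patients for whom antibiotics were already being considered.

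Finally, replacing the profile by an all-visit rate would depart from an aim that is specific to ARI and would dilute any effect. That objection holds, so the all-visit rate belongs beside the ARI-coded profile and not in its place.

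**Conclusion.** The point holds as a possibility and not as a demonstrated bias. The profile depends on a post-randomisation label given by unblinded physicians whose diagnostic reasoning on ARI is both trained and tested, and no planned measure would separate a coding change from a prescribing change across those physicians' ARI practice.

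Direction and size are unknown. The illustrated shifts, about 1 to 6 points upward and 1 to 11 downward, rest on three assumptions: a relabelled share of 5% to 20%, a profile expressed as a proportion, and relabelling that crosses the ARI code boundary.

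The consequence is confined to a secondary, exploratory outcome of a pilot. The four feasibility criteria do not use RAMQ data and are unaffected. The change is still worth making because it is cheap and protects the reading of a stated aim.

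**What to change.** Keep the ARI-coded profile as the measure for the prescription-profile aim. In Prescription profile of antibiotics in ARI, add two quantities from the same RAMQ extraction:

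1. ARI-coded visits as a share of all visits by RAMQ-drug-insured patients to the participating physicians, by arm and calendar period.
2. A supportive rate of filled antibiotic prescriptions over all such visits, by arm and in the same calendar windows.

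State the reading rule in advance: an arm difference in the ARI-coded profile is read as a prescribing effect only if the coded share is stable and the all-visit rate moves the same way.

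The cost is a wider extraction from a database already being queried, plus a table. The supportive rate also includes antibiotics for non-respiratory infections, so it is diluted. For a rough scale, the Background puts a related group of infections (without pharyngitis, but with chronic sinusitis and eustachian tube disorders) at 5.7% of primary diagnosis groups in adults and 16.3% in children under twelve. Taking these as the ARI share of visits, an illustrative true fall of 10 points in the ARI rate would move the all-visit rate by 10 × 0.057 = 0.57 points in adults and 10 × 0.163 = 1.63 points in children. The all-visit rate can therefore support a conclusion but is too insensitive to carry one, and the coded share is the more direct check on relabelling.

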#### Script Concordance Test (SCT)

Clinical reasoning is assessed with a SCT on diagnosis and management of ARI [26-31]. The same SCT is completed three times over the study period (Figure 2). In both groups, SCT are completed at the beginning of the first and at the end of the third workshop (SCT 1 and 2 in the experimental group and SCT 2 and 3 in the control group). SCT 1 in the control group is completed at baseline and SCT 3 in the experimental group at exit of the study.

#### Physicians' reactions to uncertainty

Two subscales from the Physicians' Reactions to Uncertainty questionnaire are completed at baseline: anxiety about uncertainty and disclosing uncertainty to patients [32,33].

#### Intention to engage in SDM and to use clinical practice guidelines regarding the use of antibiotics in ARI in future clinical encounters

At baseline, in reference to the theory of planned behaviour [34], FPs/GPs complete a questionnaire assessing their attitude, subjective norm, perceived behavioural control, and intention to engage in SDM as well as to use clinical practice guidelines in future clinical encounters dealing with the use of antibiotics in ARI. Physicians are also asked to complete this questionnaire at the exit of the study.

Before their clinical encounter for ARI, each participating patient is asked to complete a similar questionnaire on intention to engage in SDM in a clinical encounter dealing with the use of antibiotics in ARI.

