We are planning a large clustered randomized clinical trial (RCT) aiming at evaluating the impact of DECISION+, a continuing professional development program in shared decision making on the optimal use of antibiotics for treating ARI. We report on the study protocol of an ongoing pilot clustered randomized controlled trial (RCT) to assess the feasibility of this larger trial. Based on our conceptual framework (Figure 1), specific aims include to: 1) assess the feasibility of recruiting Family Medicine Groups (FMG), family physicians/general practitioners (FPs/GPs) and their patients, 2) develop, adapt and validate DECISION+ training workshops and related material, and 3) evaluate physicians' participation and satisfaction regarding DECISION+. Specific aims also include estimating the impact of DECISION+ on: 1) decision of both physicians and their patients regarding the use of antibiotics, 2) decisional conflict scores of both physicians and their patients as well as level of agreement between their decisional conflict scores, 3) prescription profile of antibiotics for ARI, 4) intention of physicians to implement SDM in their clinical practice, 5) intention of physicians to implement clinical practice guidelines on ARI, 6) scores obtained by physicians on a Script Concordance Test (SCT), and 7) decisional regret of patients.

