## Methods/Design

### Design

The study is a two-arm clustered RCT conducted in the Quebec City area, Canada (Figure 2). FMG is the unit of randomisation. A FMG consists in a group of family physicians who work in close cooperation with nurses to offer family medicine services to registered individuals. There are currently over 130 such groups in the Province of Quebec. FMG are randomized to either 1) an immediate DECISION+ program (experimental group) or 2) a delayed DECISION+ program (control group). Simple randomisation and concealed assignment is performed by an independent biostatistician using Internet-based software.

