### Data collection process

Data on FPs/GPs' socio-demographic characteristics, intention to integrate SDM and clinical practice guidelines on ARI in practice, and reaction to uncertainty are collected at baseline in both groups (Figure 2). Then, five patients consulting a participating physician for an ARI are recruited by a research assistant in the waiting room before the clinical encounter (Phase 1). Data on patients' socio-demographic characteristics and intention to engage in SDM when consulting for an ARI are collected at that point in time. FPs/GPs and patients are both invited to complete the Decisional Conflict Scale after the clinical encounter. Patients and FPs/GPs are blinded to the answers of the other member of the dyad. Patient recruitment and completion of the Decisional Conflict Scale by patient and physician are repeated at two weeks after the third workshop of the immediate DECISION+ group (Phase 2) and again after the third workshop of the delayed DECISION+ group (Phase 3). All patients are contacted by phone one to two weeks after their clinical encounter to complete the Decisional Regret Scale. Finally, all participating FPs/GPs complete an exit questionnaire including data on intention to engage in SDM and use of clinical practice guideline as well as on satisfaction with the DECISION+ program.

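### Physician intention is measured only at baseline and at exit, after both arms have been offered DECISION+, so its two impact aims have no randomised comparison

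*Protocol article*

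**What the plan says.** The specific aims in the Background include estimating the impact of DECISION+ on "intention of physicians to implement SDM in their clinical practice" (aim 4), and the matching intention for clinical practice guidelines (aim 5). Under Design, the comparator is "a delayed DECISION+ program (control group").

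The timing is stated twice, and the two places agree:

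- The section on intention gives physicians the questionnaire at baseline and adds: "Physicians are also asked to complete this questionnaire at the exit of the study".
- Data collection process lists physician intention among the baseline items. It then runs through Phases 1 to 3, the last of these being "again after the third workshop of the delayed DECISION+ group (Phase 3"), and closes with "Finally, all participating FPs/GPs complete an exit questionnaire including data on intention to engage in SDM". The same exit form asks about satisfaction with DECISION+.

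Sample size and analysis says that the design permits two comparisons: a randomised one of exposed against unexposed physicians and patients, and a pooled before-after one across both arms. It also plans significance tests between study groups for the secondary outcomes.

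**The concern.** In a delayed-intervention design, the randomised effect can be estimated only while one arm has been trained and the other has not. An outcome that skips this interval has no unexposed group after baseline. Physician intention is such an outcome, although two of the seven impact aims depend on it.

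Two misreadings could follow. A small between-arm difference at exit could be taken as evidence that the programme does not change intention, when a difference near zero is expected whatever the true effect. Alternatively, a rise from baseline to exit could be reported as an effect found in a randomised trial, although it cannot be separated from the passage of time or from answering the same questionnaire twice. No analysis method can recover the missing measurement afterwards.

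**Working it through.** **The plan's own figure.** Four FMG with at least 6 physicians each give 4 × 6 = 24 physicians, and 24 × 5 patients × 3 phases = 360 patients. Both totals match Sample size and analysis. The point at issue concerns timing, not sample size.

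**Exposure by arm** (1 = has been offered the full programme, 0 = has not). The timings come from Design, Data collection process and the section on intention.

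| Time | Experimental | Control | Contrast | Physician intention collected? |
|---|---|---|---|---|
| Baseline | 0 | 0 | 0 | yes |
| Phase 2, before control workshops | 1 | 0 | 1 | no |
| Exit | 1 | 1 | 0 | yes |

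Three statements place exit after the control arm's training. The exit form is described last, after Phase 3. It asks all physicians how satisfied they were with the programme. The SCT section also pairs the experimental arm's third test, taken at exit, with the control arm's third test, taken at the end of its third workshop. Figure 2 is not available here, but the text is consistent without it.

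**What the exit difference estimates.** Let d be the programme's effect on intention, the same in both arms.

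- If the effect persists fully, the expected exit difference is d − d = 0 for any d. A test of it then rejects only at its nominal error rate.
- If the earlier-trained arm keeps a fraction r of the effect (r below 1) and the later-trained arm still has all of it, the expected difference is r·d − d = −(1 − r)·d. The sign is then opposite to that of the true effect.

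Neither quantity is d.

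**Other data.** Patients answer a similar intention questionnaire before their encounter, but aims 4 and 5 concern physicians. Physicians' decisional conflict is measured in both arms at Phase 2, so the design already has an assessment point with contrast 1 from which physician intention is absent.

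**Precision of a Phase 2 contrast.** The article gives no SD, intracluster correlation (ICC) or effect size, so these are assumptions: two FMG per arm, 6 physicians each, ICC 0.01 to 0.10, total SD 1, and no gain from baseline adjustment.

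- Variance of one FMG mean = ICC + (1 − ICC)/6, which is 0.175 to 0.25.
- With two FMG per arm, the variance of the arm difference is 2 × (that value)/2, so it is the same. The SE is 0.42 to 0.50.
- On 2 degrees of freedom t = 4.303, so the 95% half-width is about 1.8 to 2.2 SD. Power for a 0.5 SD effect is about 10% to 11%.

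**The case against.** **The pilot could not estimate the effect anyway.** With four clusters, a Phase 2 difference would have the very wide interval just shown. The primary outcomes are feasibility measures, secondary outcomes are described as exploratory, and no sample size was calculated. This stands, and it limits the severity. It does not remove the point: an imprecise estimate of the right quantity differs from an estimate of something else, and impact on intention is a declared aim.

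**The before-after analysis already covers intention.** Sample size and analysis does name a pooled before-after comparison, and baseline-to-exit intention fits it. Nor does that section say that every outcome supports the randomised comparison. This stands in part. What remains is that aims 4 and 5 are worded as impact, and the claim about randomised physician data is made without excluding intention.

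**A stronger reading about the Script Concordance Test.** A reader might infer that the SCT comparison is also lost, or biased towards DECISION+, because the protocol states that "In both groups, SCT are completed at the beginning of the first and at the end of the third workshop". SCT 2 is thus taken at workshop 3 in the experimental arm and at workshop 1 in the control arm. The article does not support that reading:

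- SCT 2 does provide a randomised trained-against-untrained contrast.
- The article does not say that absentees go untested; the full protocol may provide for them.
- Absence could affect both arms, and nothing shows that attenders score higher.
- SCT 1 is available in both arms for baseline adjustment.
- The 70% feasibility criterion refers to attendance at all three workshops, not at workshop 3. If absences were equal and independent, workshop 3 attendance would be 0.70^(1/3) = 89%. With an assumed 90% of controls at workshop 1 and an assumed 0.5 SD gap between attenders and absentees, the unadjusted bias would be (0.11 − 0.10) × 0.5, or about 0.01 SD. With workshop 3 attendance anywhere from 70% to 100%, it runs from (0.30 − 0.10) × 0.5 = +0.10 to (0 − 0.10) × 0.5 = −0.05 SD.

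Neither the size nor the direction of such a bias can be fixed from the article.

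**Conclusion.** The point holds for physician intention. As scheduled, the exposed-minus-unexposed contrast is 0 at both measurements, so aims 4 and 5 have only an uncontrolled before-after change, and the exit difference between arms does not estimate the programme's effect. This follows from the stated timing and needs no assumed figure; it rests only on exit falling after the control arm's workshops, which the text supports in three ways.

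Severity is moderate. A reader might infer that the pilot's main purpose is compromised, but none of the four feasibility criteria uses intention. For the SCT only a minor precaution is warranted.

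**What to change.** 1. Give the existing physician intention questionnaire to all randomised physicians in both arms around Phase 2, before the control arm's first workshop. Name the between-arm difference at that time, adjusted for baseline and allowing for clustering by FMG, as the exploratory randomised estimate for aims 4 and 5, and say that it will be imprecise. Keep exit values for before-after and durability description.
2. The article describes the trial as ongoing. If the Phase 2 window has passed, state that physician intention supports only a non-randomised before-after analysis. Limit the aims in the Background and the comparison claim in Sample size and analysis accordingly.
3. As a minor addition, offer SCT 2 to every randomised physician in the same window, whether or not they attend the workshop, so that the comparison does not depend on attendance.

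The cost is one more administration of an existing form to about 24 physicians, a slight burden that is equal in both arms. If only the second step is still possible, it costs a change of wording.
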